### **(1) On-site Treatment Measures**

Emergency plans for SAE treatment in clinical trials shall be established at the trial site, and all relevant personnel shall be trained. If the subjects show serious adverse events, the investigators shall immediately take appropriate measures for the subjects and record them. The investigators must take relevant approaches to know in time any clinically significant diseases/events related to vaccination. According to relevant national regulations, the subjects should be received appropriate treatment in time in the designated hospitals.

Investigators at the trial site should follow up serious adverse events until the symptoms disappear or stabilize. The progress and outcome of all symptoms will be recorded in detail, and all drug treatments and medical treatments will be recorded at each follow-up. Investigators should truthfully record serious adverse events, which shall be evaluated and discussed in the final report after the test is completed or terminated.

During the whole observation process, if the subjects suffer from physical injuries caused by serious adverse reactions related to vaccination, which is confirmed by the expert investigation team, the local insurance company will give corresponding compensation.

### **(2) Reporting Procedures for Serious Adverse Events**

- Reporting procedures of investigators

Any serious adverse event, whether or not related to the investigational vaccine, the

investigator must submit the initial report of the "Serious Adverse Event Report Form" to the drug administration department, the sponsor and the ethics committee by fax, e-mail or EDC system or personal delivery within 24 hours after learning about it.

Subsequently, the follow-up report of the "Serious Adverse Event Report Form" shall be submitted regularly until the end of the event. All information is reported in the "Serious Adverse Event Report Form" in the form of written reports, including description of adverse reactions/events, onset time and type, duration, intensity, causal relationship with vaccination, results, treatment methods (symptomatic treatment) and other relevant clinical and laboratory data.

When receiving the report of serious adverse events/reactions, the investigator shall, together with the sponsor, comprehensively consider the duration, scope, intensity, outcome and the willingness of the subject to decide whether the subject should continue to participate in the study or withdraw from the study in advance.

- Reporting procedure of sponsors

During the clinical trial of drugs, sponsors need to quickly report unexpected and serious adverse reactions (SUSAR) that are definitely related to or suspicious of the tested drugs in the form of case-by-case safety reports according to the Standards and Procedures for Rapid Reporting of Safety Data during Clinical Trial of Drugs. If the researcher and the sponsor cannot reach an agreement on the judgment of the causal relationship between adverse events and drugs, either party's judgment cannot exclude those related to the test drugs, and the sponsor should also make a quick report.

For SUSAR that is fatal or life-threatening, the sponsor should report it as soon as possible after the first knowledge, but not more than 7 days, and report it within the following 8 days to improve the follow-up information (Note: the day when the sponsor first learned it is the 0th day). For SUSAR that is not fatal or life-threatening, the sponsor should report it as soon as possible after the first knowledge, but not more than 15 days. For other potential serious safety risk information, the sponsor should also report to the national drug evaluation agency as soon as possible, and at the same time make medical and scientific judgment on each situation. After the first report, the sponsor shall continue to track the serious adverse reactions and submit relevant new information or changes to the previous report in a timely manner in the form of a follow-up report. The reporting time limit shall be within 15 days from the date of obtaining the new information.

---

#### **8.4. Outcome of Serious Adverse Events**

The outcomes of serious adverse events include: (1) Symptoms resolved (with sequelae); (2) Symptoms resolved (no sequelae); (3) Symptoms persist; (4) require hospitalization; (5) require medical intervention to prevent serious outcomes; and (6) death.

### **9. COMPLETION OF CLINICAL TRIAL**

After obtaining the immunogenicity test results 28 days after the full course of immunization, and completing the safety follow-up for no less than 1 month, and ensuring the authenticity, integrity and accuracy of clinical trial data, the database is locked and unblinded to perform safety, immunogenicity and vaccine efficacy evaluation, and blood collections for 12 months immune persistence are completed, the study site will be closed.

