### **6.1.1 Investigational Vaccine**

Investigational Vaccine: Recombinant COVID-19 Vaccine (CHO cell)

Manufacturers: Sinopharm CNBG National Vaccine and Serum Institute (NVSI),  
Lanzhou Institute of Biological Products Co., Ltd. (LIBP)

Specifications: 0.5 ml/vial per human use, which contains 20ug of viral protein antigen.

Storage Condition: 2-8 °C.

Vaccine Batch Number: 20201113

Expiry Date: Nov 11, 2022

Control vaccine: Inactivated COVID-19 Vaccine (Vero cell)

Manufacturer: Beijing Institute of Biological Products Co., Ltd.

Specifications: 0.5 ml/vial per human use, which contains 6.5U of antigen.

Storage conditions: 2-8 °C

Vaccine Batch Number: 2021071710.

Expiry Date: Jul 8, 2023

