## **6.2 Vaccine Packaging and Labeling**

All investigational vaccines are packaged in doses in boxes with the same appearance and only marked by the vaccine number. Each study ID will be matched with a unique vaccine number, the format of the vaccine number is AE+4-digit Arabic number. See the following label for detailed information.

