##### Vaccine Label:

|                                               |
|-----------------------------------------------|
| Recombinant COVID-19 Vaccine(CHO cell) |
| (For Clinical Use Only)                |
| Vaccine Number: AExxxx                        |
| Batch Number: XXXX                            |

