### **6.3.3 Vaccine Records**

*Vaccine handover records:* The sponsor will provide investigational vaccines, control vaccines (placebo) and vaccine handover sheet, and investigator will verify the name, batch number and quantity of the vaccine upon receiving.

*Vaccine registration and use records:* the investigator shall establish vaccine registration and use records and distribute investigational vaccine and control vaccines according to the number of people in the observation groups.

*Vaccine recycle record:* The abandoned, expired and the remaining vaccines in this trial are returned to sponsor. Sponsor receives vaccines and verifies the batch number and quantity of vaccines, fills in the vaccine handover form, and makes relevant records, which are signed by vaccine manager and sponsor representatives

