## **7.3 Safety Observation and Follow-up**

### **7.3.1 Safety Observation**

(1) Observe the site for 30 minutes after vaccination to collect local and systemic adverse events.

(2) Telephone follow-up once in 6-24 hours after vaccination, within 1-3 days and 4-7 days respectively, the subjects were followed-up by telephone and guided to observe the adverse events

correctly and fill in the diary card.

(3) On the 14th day (Visit 4), the investigator reviews the filling of the diary card during this period and re-collect the diary card.

(4) On the 8th -30th day after vaccination, the investigator uses telephone follow-up once a week, combined with active report of the subjects to monitor the safety.

(5) When it is known that the subject has adverse reactions/events of Grade 3 or above, a face-to-face visit should take place within 24 hours.

(6) SAEs and AESIs are observed from the first dose to 6 months after the full course of vaccination by means of monthly telephone follow-up and self-reports from the subjects.

Note: Subjects should report respiratory tract infection symptoms such as fever and cough. Investigators should make comprehensive judgments, carefully identify whether it is common solicitation symptoms after vaccination or infection caused by other reasons, and closely observe the disease progress. Once the disease worsens, report it to the person in charge of the site quickly, and start the green treatment channel quickly to ensure that the subjects get timely diagnosis and treatment.

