## **8. SAFETY DEFINITION, REPORTING AND MONITORING**

### **8.1 General Precautions**

This clinical trial is a randomized, double-blind and controlled trial design.

Before the start of the trial, the sponsor shall strictly examine the trial site in accordance with GCP requirements, focusing on whether the environmental facilities of the trial site meet the requirements of "Vaccination Management Standards" and "Guiding Principles for Quality Management of Vaccine Clinical Trials". Ensure the first aid facilities and first aid equipment in the first aid room are complete and effective, and the first aid doctors have corresponding qualifications and capabilities. Emergency related personnel (emergency doctors, emergency nurses, ambulance drivers, etc.) are trained to be qualified and familiar with the transfer routes and procedures of the agreed hospital. They are on standby at the trial site during vaccination. The trial site shall be equipped with ambulances. The ambulance shall be parked in a fixed position to keep the vehicle in good condition and in an emergency and shall be under the command and transfer of the emergency response team at any time. During the vaccination period, the agreement hospital will make daily preparations for medical personnel, instruments and equipment, first aid drugs and first aid sites to ensure that the subjects can receive timely treatment. The trial site shall formulate an emergency plan, stipulate personnel responsibilities, contact numbers, rescue routes and other measures to ensure timely handling of unexpected adverse events, and ensure effective contact between subjects and investigators so that any adverse events can be reported and handled quickly.

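### Arm-specific batch numbers on the label template, and unblinding at the day-28 lock, leave the double-blind unprotected for safety, case and persistence data; sections 6.2, 6.3.3, 4.6.2, 7.8 and 9 need reconciling

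*Protocol*

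**What the plan says.** **Declared blinding.** Section 8.1 states: "This clinical trial is a randomized, double-blind and controlled trial design". Section 4.1 and the synopsis say only that the trial is blinded.

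**Labels.** Section 6.2 describes vaccine "packaged in doses in boxes with the same appearance and only marked by the vaccine number". The label illustrations in section 6.2.1 show more than that. The outer box has a batch number field, and the vial label reads "Batch Number: XXXX". Section 6.1.1 lists one batch for each product: "Vaccine Batch Number: 20201113" for the recombinant vaccine and "Vaccine Batch Number: 2021071710" for the inactivated control. Under section 6.3.3 the investigator checks name, batch number and quantity on receipt, and is then to "distribute investigational vaccine and control vaccines according to the number of people in the observation groups". Under section 7.2.1 both labels are checked before the injection.

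**Lock and follow-up.** Section 9 sets the trigger as the day-28 immunogenicity results plus at least one month of safety follow-up; at that point "the database is locked and unblinded to perform safety, immunogenicity and vaccine efficacy evaluation". Section 4.6.2 keeps the subject and vaccine lists sealed until the database is locked. Section 7.3.1 says "SAEs and AESIs are observed from the first dose to 6 months after the full course of vaccination". Section 7.4 schedules the last blood draw at day 360 (+30). Section 7.8 puts a blind audit by the statistician after the 6-month safety and 12-month blood collection.

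**The concern.** The protocol contains two separate routes by which allocation can become known to people who still generate or judge data.

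The first is the label. With one batch per arm, a true batch number on the box or vial is equivalent to the arm, and the key is printed in the protocol that the site holds. Diary-card reactions, the five-level causality rating of section 4.5.3 and unsolicited event reports all depend on someone's judgement. Safety is a secondary objective, and section 10.3.4 compares the arms by Fisher's exact test.

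The second is the lock. Once the code is opened after day 28, no sentence limits who receives it or says who stays masked. SAE/AESI reporting and causality, symptom-triggered PCR testing (Table 4, note 5), COVID-19 case ascertainment for the exploratory efficacy objective, and the persistence assays all continue. Section 7.8 assumes the data are still blind at a time when section 9 has already unblinded them.

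**Working it through.** There is no stated figure to reproduce. The check compares passages and counts the follow-up left at lock.

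**1. Labels, side by side**

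| Source | Content |
|---|---|
| 6.2 | same-looking boxes, vaccine number only |
| 6.2.1 illustrations | vaccine number and batch number, on box and vial |
| 6.1.1 | recombinant 20201113 (8 digits); control 2021071710 (10 digits) |
| 6.3.3 | investigator verifies batch number on receipt |
| 7.2.1 | box and vial labels checked at vaccination |

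Section 6.2 and its own illustration cannot both hold. If the batch field holds the true number, the arm follows directly. No masked lot code and no unblinded site pharmacist or vaccinator is described; the unblinded staff of section 4.6.2 act before the study starts.

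**2. Reach of the label route.** It touches site staff and possibly subjects from day 0. It does not reach the serology: sections 7.4 and 11.6 identify samples by study or subject code, sample number, time and test only.

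**3. Follow-up left at lock.** For a subject *t* days after vaccination at lock:

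- SAE/AESI days left = max(0, 180 − *t*)
- persistence days left = 360 − *t*
- draws left = number of {90, 180, 270, 360} greater than *t*

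For the last subject vaccinated:

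| Lock | SAE/AESI left | Persistence left | Draws left |
|---|---|---|---|
| D30, earliest | 180 − 30 = 150 of 180 (83%) | 360 − 30 = 330 of 360 (92%) | 4 of 4 |
| D68 = 28 + 10 (window) + about 30 (testing); assumed timing | 180 − 68 = 112 of 180 (62%) | 360 − 68 = 292 of 360 (81%) | 4 of 4 |

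**4. All subjects.** This needs the vaccination span *S*, which the protocol does not give. I assume uniform accrual and a single lock one month after the last dose, so that *t* is spread evenly from 1 to 1 + *S* months. Mean SAE/AESI follow-up left is the average of max(0, 6 − *t*).

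- *S* = 1 month (the recruitment period in section 7.7, Study Duration, if vaccination keeps pace): *t* runs from 1 to 2, and 4 to 5 months are left; mean 4.5 of 6 (75%). All four draws lie ahead for everyone.
- *S* = 5 months (18 months minus 12 and a 1-month window): 12.5 / 5 = 2.5 of 6 months (42%).
- *S* = 6 months (18 − 12): 12.5 / 6 ≈ 2.1 of 6 months (35%).

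With *S* of 5 to 6 months, the earliest subjects are 6 to 7 months past vaccination at lock. They have finished or nearly finished the 6-month safety period and have reached the 3- and 6-month draws. The 9- and 12-month draws still lie ahead for every subject.

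**5. Reach of the lock route.** The day-14 and day-28 samples are drawn and tested before the trigger in section 9, so the co-primary titres cannot be influenced by it. Everything collected afterwards can.

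**The case against.** The best case for the plan has five parts.

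- **The label is an illustration with a placeholder.** The batch field is blank or XXXX, and nothing says the true lot will be filled in. The one product name shown, that of the recombinant vaccine, may be meant for both arms. This stands. A reader might infer that all 1,800 doses are unblinded, but the documents support that only if true batch numbers are printed. The contradiction with section 6.2 remains either way.
- **Section 6.3.3 is ambiguous.** Observation groups could mean stock quantities or the three interval cohorts, and individual doses are allocated by IWRS under section 4.6.1. It is therefore not an instruction to hand out vaccine by arm. It still sits badly with blinded allocation and should be reworded.
- **Coded samples and early co-primaries.** A reader might infer bias in the primary titres or in cytopathic-effect readings made from labels. The documents do not support this: samples are coded, and the co-primary data precede the lock. For the laboratory, only persistence assays after the lock are open to question.
- **Section 9 might mean a single lock at 12 months.** Section 7.8 assumes blind data then, section 10.5 plans no interim analysis, and section 7.7 (Study Duration) lists the report after persistence. But section 9 ties lock and unblinding to the day-28 results and attaches the 12-month draws to site closure. At best this shows that the sections disagree.
- **A day-28 primary analysis is legitimate, and access rules may sit in a document not shown.** Both are fair. Another document could supply the access rule, but it would not remove the conflict within this protocol.

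**Conclusion.** The point holds as a conflict within the protocol and a gap in protecting the blind, not as a demonstrated break of it.

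The label limb is conditional: if true batch numbers are printed, the arm is readable from day 0, and the day 0–30 adverse event and causality data are exposed. The lock limb rests on the natural reading of section 9 together with section 4.6.2. Up to 150 of 180 SAE/AESI days and all four persistence draws then fall after the earliest lock for the last subject vaccinated.

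A reader might take about five of six months as the exposure of every subject. That is the upper end. Averaged over subjects it is roughly 2.1 to 4.5 of 6 months, depending on an assumed vaccination span of 6 down to 1 month, with a single lock and even accrual. The non-inferiority conclusion on day-14 and day-28 titres is not threatened by the lock. Later SAE/AESI reporting and causality, COVID-19 case ascertainment and persistence data are. The change should be made, because it is cheap and the trial is declared double-blind.

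**What to change.** 1. **Sections 6.2 and 6.2.1.** Remove the batch number from box and vial labels, or print one common coded batch, with identical product wording on both arms. Keep the true batch list with the unblinded staff of section 4.6.2.
2. **Section 6.3.3.** Reword so that receipt checks and distribution go by IWRS vaccine number, not by product, true batch or group.
3. **Sections 4.6.2, 7.8 and 9.** Align them. At the day-28 lock, subject-level allocation goes only to the analysts who run that analysis. Sites, subjects, the laboratory and those who assess adverse events and COVID-19 cases stay masked until the 12-month lock, so that the audit in section 7.8 is in fact blind.

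The cost is new label artwork, edits to these sections and an access restriction on the day-28 outputs. Sample size, endpoints and visits do not change.

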### **10. STATISTICAL CONSIDERATIONS**

#### **10.1 Sample Size Considerations**

Assume 4-fold rise rate after sequential vaccination achieve 85%, 208 subjects in each arm will be required to have 80% power to conclude non-inferiority with margin of -10% and one-sided significance level of 2.5% using Miettinen & Nurminen method.

Equal GMT after sequential immunization is assumed, and standard deviation of GMT after log10 transformation is considered to be 0.7. 250 subjects in each arm will be required to have 80% power to conclude non-inferiority with margin of 2/3 and one-sided significance level of 2.5%.

Considering about 15%~20% drop-out rate, 600 subjects in three sequential cohorts (1-3 months, 4-6 months and ≥6 months after 2 doses), and 1800 subjects (900 subjects in test and control groups respectively) in total are planned to enroll.

#### **10.2 Analysis Set**

Full Analysis Set (FAS): It includes all randomized participants who follow ITT principle, receive 1 dose of vaccine, and have valid immunogenicity data before the first dose.

Per-Protocol Set (PPS): It includes all participants who do not violate the inclusion criteria/exclusion criteria, receive 1 dose of vaccine, and have both valid pre- and post-vaccination immunogenicity data. PPS will be defined for immunogenicity evaluations 14 and 28 days after sequential vaccination, respectively.

Immunogenicity Persistence Set (IPS): It include the participants who are collected

with blood samples at each time point for immunogenicity persistence evaluation and with valid antibody data. Define the IPS for immunogenicity for 3, 6, 9, 12, 18 and 24 months after sequential immunization respectively.

Safety Set (SS): It includes all participants who receive one dose of vaccination.

In immunogenicity analysis, the participant who takes the vaccine erroneously will be included as randomized, and the safety data will be analyzed as treated.

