## 7.5 Concomitant Medication

Within 0-30 days, actively follow up and observe the local and systemic adverse events of the subjects and record them on the vaccination diary card. At the same time, it is necessary to record the drug used of the subjects in the vaccination diary card.

**Medication Allowed:** During the clinical trial, if the subject has adverse events, necessary medication and medical treatment should be allowed.

**Vaccines Allowed:** Other vaccines are allowed during the trial, which should be carried out 14 days after the trial vaccination. Emergency vaccination, such as rabies vaccine and tetanus vaccine, is not restricted.

**Medication Record:** To understand the influence of drug use during the trial on vaccine safety and immunogenicity, and to collect adverse events that may be related to vaccination without omission, investigators should instruct the guardians of the subjects to record the medical treatment and medication in diary cards as much as possible and assist in collecting the hospitalization medication records of the subjects during the observation period. When SAE occurs, copies of corresponding medical records and medication records should be collected and kept. The following drugs need to be transcribed into the electronic case report form (eCRF).

- (1) Hormone/steroid drugs and other immunosuppressants.
- (2) Antiallergic Drugs
- (3) Antipyretics/analgesics/NSAIDs
- (4) Prophylactic Vaccines
- (5) Therapeutic Medical Products
- (6) Antibiotics
- (7) Antiviral Drugs
- (8) Chinese Patent Drugs
- (9) Others

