## **7.7 Protocol Violation and Deviation**

### **7.6.1 Protocol Violations**

The list of protocol violations is as follows (including but not limited to):

- Fail of obtain subject's informed consent;
- Subjects who did not meet the inclusion criteria or met the exclusion criteria were enrolled in the study;
- Subjects received wrong research interventions (such as vaccination errors);
- Fail to report serious adverse events (SAE) within specified time;
- Received other investigational vaccines during the study period.

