### **7.6.2 Protocol Deviations**

The list of protocol deviations is as follows (including but not limited to):

- Not receive the investigational vaccine during the window period;
- Not collect blood during the window period;
- The interval between vaccination and other vaccines is not long enough, except for emergency vaccination such as rabies.

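### The per-protocol set keeps wrong-vaccine recipients in their randomised arm, which tilts the non-inferiority tests slightly towards success

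*Protocol*

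**What the plan says.** Section 10.2 defines the PPS by three conditions: no breach of the eligibility criteria, and participants must "receive 1 dose of vaccine, and have both valid pre- and post-vaccination immunogenicity data". The section closes with a rule for vaccination errors: "In immunogenicity analysis, the participant who takes the vaccine erroneously will be included as randomized". Safety data, by contrast, are analysed by the vaccine actually received. The rule speaks of immunogenicity analysis as a whole and does not separate the FAS from the PPS.

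Section 7.6.1 puts this event on its list of protocol violations: "Subjects received wrong research interventions (such as vaccination errors". Section 7.6.2 lists a related deviation: "Not collect blood during the window period". Section 10.2 refers to neither list.

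The tests at stake are non-inferiority tests. Sections 4.4 and 10.3.3 set a margin of −10 percentage points for the 4-fold rise and a margin of two thirds for the GMT ratio. Section 10.6 requires both to be met.

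**The concern.** In a superiority trial, counting people in the arm they were randomised to is the cautious choice. In a non-inferiority trial it is not, because anything that makes the arms look alike helps the new product. The PPS is the usual safeguard: it asks whether the conclusion stands among people who received what they were assigned.

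Under section 10.2 the PPS cannot do this for vaccination errors. A participant who meets the eligibility criteria, has one dose of the wrong vaccine and gives valid samples passes all three conditions and is counted under the arm whose vaccine was not given. On this point the FAS and the PPS carry the same dilution, so agreement between them would not reassure. The protocol also treats the event as a violation in one section and as per protocol in another.

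**Working it through.** **Inputs.** From section 10.1: 80% power with "margin of -10% and one-sided significance level of 2.5% using Miettinen & Nurminen method"; "Assume 4-fold rise rate after sequential vaccination achieve 85%, 208 subjects in each arm will be required to have 80% power"; equal GMTs; standard deviation on the log10 scale, after "transformation is considered to be 0.7"; GMT margin two thirds with 250 per arm; drop-out 15% to 20%; 900 per arm in total. The crossover share c is an assumption, because the protocol gives no rate of vaccination errors.

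**Step 1: reproduce the plan's figures.** GMT: n = 2 × (1.960 + 0.842)² × 0.7² / 0.176² gives 249 per arm by the normal approximation. The noncentral t gives 250 (power 0.8015). The stated figure is 250. For the 4-fold rise, 85% in both arms and a 10-point margin give 206.9, so 207, by the score formula that is the large-sample form of the stated method. The stated figure is 208. Neither sample size is in dispute.

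**Step 2: effect of crossover.** Let T and C be the mean log10 titres produced by the two vaccines, and let a share c of each arm receive the other vaccine. Analysed as randomised:

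- test arm mean = (1 − c)T + cC
- control arm mean = (1 − c)C + cT
- observed difference = (1 − 2c)(T − C)

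The same factor applies to a difference in response rates. With unequal shares a and b the factor is 1 − a − b.

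**Step 3: type I error at the margin.** Put the true effect at the margin, where the error should be 0.025. The one-sided error is Φ((observed difference + margin)/SE − 1.960). For GMT the margin is 0.1761 on log10 and SE = 0.7 × √(2/n).

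Example, c = 1% and n = 250:

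- SE = 0.0626
- observed difference = −0.98 × 0.1761 = −0.1726
- (−0.1726 + 0.1761)/0.0626 = 0.056
- Φ(0.056 − 1.960) = 0.0285

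Two sizes are shown. One is 250 per arm, which is about one cohort. The other is about 750 per arm for the pooled comparison, since 900 less 15% to 20% leaves 765 to 720.

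| c (assumed) | Factor | True GMT ratio 0.667 seen as | True −10 points seen as | Error, 250 per arm | Error, about 750 per arm |
|---|---|---|---|---|---|
| 0 | 1.00 | 0.667 | −10.0 | 0.0250 | 0.0250 |
| 0.5% | 0.99 | 0.669 | −9.9 | 0.0267 | 0.0280 |
| 1% | 0.98 | 0.672 | −9.8 | 0.0285 | 0.0313 |
| 2% | 0.96 | 0.678 | −9.6 | 0.0323 | 0.0388 |
| 5% | 0.90 | 0.694 | −9.0 | 0.0466 | 0.0704 |

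The error columns are for GMT. The 4-fold rise (85% against 75%) gives the same values to this precision.

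**Step 4: reading the table.** These are errors for each endpoint separately. Because section 10.6 requires both, the chance of a false overall conclusion cannot exceed the value for an endpoint that truly sits at its margin. Removing crossed-over participants from the PPS returns each figure to 0.025.

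**The case against.** **Few errors are likely.** Section 4.6.1 assigns vaccine numbers through the interactive web response system, and section 7.2.1 has labels checked before injection. At 1%, which is 9 of 900 per arm, the bias is slight. This stands, and it limits the size of the point. It does not justify the rule.

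**The single dose could be read as the assigned vaccine, or the statistical analysis plan could exclude these people.** The PPS text does not say the dose must be the assigned one, and the closing sentence says wrong-vaccine recipients are included. A later plan that excluded them would depart from the protocol's own words.

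**A stronger reading is tempting.** A reader might infer that the PPS and the immunogenicity persistence set (IPS) also keep out-of-window bloods and titres after infection or a further vaccine, and that all of this dilutes the comparison. Section 7.5 does say "Other vaccines are allowed during the trial, which should be carried out 14 days after the trial vaccination", and COVID-19 is an exclusion at entry only. The documents still do not support that reading, for four reasons:

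- Both sets require valid data, and the word is not defined. It could exclude such samples, and a separate analysis plan, not seen here, may say so. Retention is inferred from silence.
- Another investigational vaccine is a violation (7.6.1) and a ground for early withdrawal (5.1.3), so some of these titres may drop out anyway.
- No non-inferiority test is stated for months 3 to 12. In the IPS the possible harm is bias in persistence estimates.
- Of these mechanisms, only crossover is certain to shrink the difference. Infections or late bloods that are unequal between arms could move it either way.

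**Conclusion.** The point holds for wrong-vaccine recipients in the PPS. The rule is explicit, it contradicts the violation list in section 7.6.1, and its bias runs towards non-inferiority. Its size rests entirely on the assumed crossover share. At 1% per arm the one-sided error is 0.0285 to 0.031 instead of 0.025; at 5% it is 0.047 to 0.070. The calculation assumes equal shares in both arms, crossover unrelated to response, and a standard deviation of 0.7. System-assigned vaccine numbers make the low end more plausible, so the practical effect is probably small. The reason to change the text is that a PPS built this way cannot serve as a check on dilution by vaccination errors.

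The handling of out-of-window samples and of titres after infection or a further vaccine is a matter for clarification only, because the plan does not state that they are kept.

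**What to change.** In section 10.2:

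1. Limit the as-randomised rule to the FAS.
2. Add to the PPS the condition that the participant received the assigned vaccine.
3. Report the non-inferiority results in the FAS and the PPS side by side.

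The cost is a change of wording and a few fewer PPS participants: 9 per arm of 900 if the rate were 1%. It should be made before unblinding.

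As a secondary clarification, state whether valid data in the PPS and IPS exclude samples outside the window, and titres after a confirmed SARS-CoV-2 infection or a further COVID-19 vaccine. For the IPS this is not only a matter of wording. Table 4 schedules concomitant medication, which under section 7.5 includes vaccines, only up to the 6-month visit, and its footnote ties follow-up PCR to symptoms. A rule reaching the 9- and 12-month samples would need further data collection. Excluding titres after infection also selects on an event that the vaccine may influence, so the text should say what the persistence estimate is meant to describe.
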